#### Hypothesis H1

Compared to walking in an urban built environment, taking a walk in a forest leads to a stronger increase in stress reduction (1), restoration (2), positive affect (3), attention (4), nature connectedness (5), and rumination (6) as well as a stronger decrease in negative affect (7).

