#### H2

Compared to walking in an environment with high road traffic noise, taking a walk in an environment with low road traffic noise leads to a stronger increase in the outcome variables 1–6 as well as a stronger decrease in negative affect.

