#### H3

Compared to walking in a forest with high road traffic noise, taking a walk in a forest with low road traffic noise leads to a stronger increase in the outcome variables 1–6 as well as a stronger decrease in negative affect.

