### Outcomes

#### Primary outcomes

The primary outcomes are “perceived restoration”, measured with a self-report questionnaire and salivary cortisol as a physiological stress marker.

Perceived restoration will be assessed using a slightly modified version of the restoration outcome scale (ROS) [67]. The questionnaire was put in past tense, and participants will be asked to what extent the walk contributed to three items concerning relaxation and calmness (e.g., “I feel calmer after being here”), one item reflecting attention restoration (“my concentration and alertness clearly increased”), and two items indicating clearing one’s thoughts (e.g., “I was able to forget my everyday worries here”). The questionnaire has been translated into German, including a back translation into English by the internal translator of the Swiss Federal Research Institute WSL. Items are rated on a Likert scale ranging from 1 (*not at all*) to 7 (*completely*). The scale has been used in several previous studies examining the benefits of exposure to nature [14, 68, 69] and has been shown to have good internal consistency with a Cronbach’s alpha of .92 [67].

The physiological stress marker salivary cortisol is considered a reliable indicator for assessing hypothalamic pituitary adrenocortical (HPA) axis activity [62, 70]. Saliva samples will be collected using synthetic swabs (Sarstedt, Germany). For saliva collection, participants will place the swab in their mouth for 2 min before returning it to the salivette collection tube. The salivettes will be put in a portable cooler immediately after saliva collection and stored there until the end of the walk. When returning from the field, saliva samples are frozen and stored at − 20 °C until analysis. The samples will be analyzed by the laboratory of [name]. [name] at the Technical University of Dresden, Germany, to determine cortisol levels. After thawing, the samples will be centrifuged at 3,000 rpm for 5 min to obtain a clear supernatant of low viscosity. Salivary concentrations are measured using a commercially available chemiluminescence immunoassay with high sensitivity (Tecan – IBL International, Hamburg, Germany; catalog number R62111).

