### Sample size calculation

A statistical power calculation was conducted for the restoration outcome scale as the primary outcome. A previous study, employing a similar design to the current study, was conducted by Tyrväinen et al. [14], who compared the restorative effects of exposure to a forest, a park, or an urban built environment using the restoration outcome scale. Participants sat in the respective environment for 15 min, followed by a 30-min walk. Based on the mean scores and standard deviations for the restorative outcome scale before and after the walk in the urban built environment and in the forest, reported by Tyrväinen et al. [14] (mean ROS urban built before = 4.56 (SD = 0.89), mean ROS urban built after = 4.2 (SD = 0.97), mean ROS forest before = 4.6 (SD = 0.84), mean ROS forest after = 5.16 (SD = 0.82)), the power for the current study was calculated using a simulation-based approach. For the simulation, a linear mixed effects model was used, taking group effects and participant effects into account by including a random intercept for participant groups as well as for individual participants. The required number of groups was estimated for a desired statistical power of ≥ 80%, calculating the number of simulations with a significant interaction effect of environment × time using R [100]. Power calculation showed that 19 groups with 1–6 participants per group are required to identify statistical differences between the conditions, assuming a power of ≥ 80% and an alpha level of 0.05. Thus, to accomplish an equal number of groups in urban built environments and forests, we are aiming for a minimum of 10 groups in urban built environments and 10 in forests.

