To include road traffic noise as a predictor in the statistical model, the audio files recorded during every walk will be checked by listening to every recoding and categorizing each one-second time period in which road traffic noise is the dominant sound source. We will then calculate the *L*_Aeq_ (equivalent continuous sound level) for the cumulative time periods in which traffic noise is the dominant sound source as well as the cumulative duration in seconds in which traffic noise is dominant. Next, we will calculate the proportion of time in which road traffic noise is not the dominant sound source in relation to the total time of the recording. Then, we will compute the* L*_AE_ (sound exposure level) for the cumulative time periods in which traffic noise is dominant. Further, we will calculate the L_AE_ for the time periods when traffic noise is not dominant, using 30 dB for times when traffic noise is not dominant. This will result in a *L*_AE_ value including *L*_AE_ when traffic noise is dominant and *L*_AE_ for time periods when traffic noise is not dominant, as well as a corresponding *L*_Aeq_ value including times when traffic noise is dominant and not dominant. Noise will be included in the model as a combined predictor of *L*_AE_ including times when traffic noise is dominant and not dominant and the proportion of time, during which traffic noise is not dominant or by using the *L*_Aeq_ including times when traffic noise is dominant and not dominant. We plan to conduct a first model with vegetation and noise as categorial predictors (forest-urban built; high-low traffic noise) and a second model including noise as a continuous and vegetation as a categorial predictor.

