In both models, we will specify fixed effects for conditions (vegetation and noise) and time (before and after the walk). Further, we will include an interaction term between vegetation and noise, as well as a random intercept term accounting for individual differences (one per subject). Additionally, in both models, the group constituting the experimental unit in this study will be entered as a second random intercept (one per group) to account for the hierarchical structure of the data due to the organization of participants into different groups. Since we will be conducting group walks, individuals will be subsamples of the walking groups, and the treatment will be applied to groups, not to individual participants. Therefore, the following model will be used: $$outcome \sim vegetation\times noise (1 |\mathrm{ group}/\mathrm{ subject})$$. If suitable, further exploratory models will be computed. For all analyses, we will set the significance level at .05 and analyses will be conducted with R [100] and R package lme4 [103].

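### With .05 for every analysis, two primary outcomes, unranked hypotheses and no decisive model, family-wise error is uncontrolled: roughly 10% to 42%, depending on what counts as success

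*Protocol article*

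**What the plan says.** All places are in the protocol article.

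- **Error level.** Data processing and statistical analysis: "For all analyses, we will set the significance level at .05". No split, order or adjustment is given.
- **Primary outcomes.** Primary outcomes names two, perceived restoration and cortisol: "measured with a self-report questionnaire and salivary cortisol as a physiological stress marker". There is no success rule.
- **Sample size.** "A statistical power calculation was conducted for the restoration outcome scale as the primary outcome". The calculation targets the environment × time interaction, with 80% power "and an alpha level of 0.05". Cortisol is not powered.
- **Hypotheses.** H1 (forest against urban built), H2 (low against high noise), H3 (noise within forest) and H4 (noise within urban built) are directional and cover every outcome. H2 reads "taking a walk in an environment with low road traffic noise leads to a stronger increase in the outcome variables 1–6" and H3 reads "taking a walk in a forest with low road traffic noise leads to a stronger increase in the outcome variables 1–6". None has priority.
- **Models.** One model has categorical noise and one has continuous noise. Neither is called primary.
- **Noise predictor.** "Noise will be included in the model as a combined predictor of" L_AE and the proportion of time without dominant traffic noise; the same sentence then offers whole-walk L_Aeq as an alternative, with no rule for choosing. Characterization of the final test sites and the Discussion describe a further version: the percentage of time traffic dominates, with the L_Aeq of that time only.

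**The concern.** A confirmatory claim needs one answer to the question of which test decides. Here a reader of the results cannot tell whether success means ROS, cortisol, either or both; which of H1 to H4 carries the claim; or which model it comes from. Any one significant result among these could be reported as confirming the study's hypothesis, with an error rate above the stated 5%.

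The choice of model has substance. The Discussion concedes that noise level is confounded with setting unless the model accounts for it, and offers the continuous-noise model as the remedy. It does not say that this model decides H1. The two models can give different answers on H1, so leaving the choice open leaves the main conclusion open.

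**Working it through.** **1. The plan's own figure.** Inputs from Sample size calculation: ROS 4.56 (SD 0.89) to 4.2 (0.97) in urban built, and 4.6 (0.84) to 5.16 (0.82) in forest.

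- Difference in change: 0.56 − (−0.36) = 0.92.
- SD of change, taking pre–post correlation r = 0: √[(0.89² + 0.97² + 0.84² + 0.82²)/2] = √(3.111/2) = 1.247.
- n per arm = 2(1.960 + 0.842)² × 1.247²/0.92² ≈ 29. With a mean group size of 3.5 (sizes 1–6 taken as equally likely), 58/3.5 = 16.6 groups, or 19.3 if the intraclass correlation of change is 0.05.
- Simulated power with 19 groups: 83.6% at r = 0 and no clustering, 93.6% at r = 0.3.

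The stated 19 groups are consistent with these inputs. They cannot be confirmed exactly, because r and the group variance are not given. They concern one outcome and one contrast only.

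**2. Family-wise error if tests were independent.** 1 − 0.95^k:

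- k = 2 (H1 on two primaries): 9.75%
- k = 8 (H1 to H4 on two primaries, one model): 33.7%
- k = 16 (both models): 56.0%

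**3. Family-wise error allowing for overlap.** H2 is built from H3 and H4, and both models use the same data, so independence is too pessimistic. A null simulation was run on group-level change scores, with 5 or 12 groups per cell, correlation between outcomes 0 or 0.3, 6,000 runs, and two-sided tests at .05. Noise levels were the Table 2 site means with an assumed scatter of SD 2 dB. The second noise metric was represented by the first plus error of SD 3 dB.

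| What may count as success | Chance of at least one false positive |
|---|---|
| H1, either primary, categorical model | 9–10% |
| H1–H4, either primary, categorical model | 27–29% |
| As above, adding the continuous model with one metric | about 37% |
| As above, free choice between two metrics | about 42% |
| Last row, hypothesised direction only | about 24–25% |

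The last row should be read against 2.5%, the rate of one two-sided .05 test in one direction. On that scale H1 on two primaries gives 1 − 0.975² = 4.94%.

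**4. Why the model matters for H1.** Averages of the three site means in Table 2: urban-high 66.14, urban-low 54.90, forest-high 61.03, forest-low 49.88 dBA. Urban averages (66.14 + 54.90)/2 = 60.52 and forest (61.03 + 49.88)/2 = 55.46. The categorical forest–urban contrast therefore carries about 5 dB of noise.

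**5. Cost of a stricter level.** A test with exactly 80% power at .05 has 1.960 + 0.842 = 2.802 standard errors of signal. At .025 its power is Φ(2.802 − 2.241) = Φ(0.561) ≈ 71%; at .0125 it is Φ(2.802 − 2.498) = Φ(0.304) ≈ 62%. For ROS at r = 0 without clustering, n per arm rises from 29 to 35 at .025, which is 70/3.5 = 20 groups.

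**The case against.** Much can be said for the plan. The sample size section points to ROS and environment × time as the lead test. The second model exists to deal with confounding, not to give another chance of significance. A journal article may leave a multiplicity procedure to a fuller document, and the models are described as prespecified. If both primaries had to succeed, no correction would be needed.

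Of this, the lead role of ROS and the purpose of the second model stand and should be built on. But the sample size section conflicts with the naming of two primaries, no rule requires both to succeed, and .05 for all analyses is a stated choice, not an omission. A fuller plan would have to resolve these points.

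Stronger readings are tempting but unsupported:

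- **That a positive result is likely to be chance.** Only the 56% figure passes one half, and it treats 16 overlapping tests as independent. All these figures are error rates under a global null, not the probability that a given finding is false.
- **That the noise metric adds a further planned test.** The text gives alternatives for one predictor. It is an unfixed choice, and nothing shows that it will be made after seeing the fit.
- **That the proportion of time is redundant because whole-walk L_Aeq contains it.** Traffic dominant all the time at 55 dB, and for 10% of the time at 65 dB with 30 dB otherwise, both give about 55 dB. The proportion cannot be recovered from L_Aeq. L_AE and L_Aeq differ by a constant (10·log10(1800) = 32.55 dB) only if every recording lasts the same time, and the pace is given only approximately.

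**Conclusion.** The point holds as a defect in what the plan fixes. It has one error level for everything, two sections that disagree on whether there are one or two primary outcomes, unranked hypotheses, no decisive model and an open noise predictor. The 10% figure for H1 is the firmest, because it needs only two primaries with either counting as success. The higher figures depend on how many hypotheses, models and metrics may count, and on the assumed noise scatter and stand-in second metric. Three further assumptions apply: tests are two-sided, since sidedness is not stated; stress reduction in the hypotheses is read as cortisol; and tests are made on the change from t1 to t2, although the printed model formula has no time term. This merits correction but does not undermine the design.

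**What to change.** Before the final analysis:

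1. Reconcile Primary outcomes with Sample size calculation, stating whether ROS is the sole primary outcome or one of two.
2. Name one confirmatory hypothesis, with H1 the natural choice as the powered contrast, and the one model that decides it. Give the reason in light of the confounding acknowledged in the Discussion.
3. Control the error over the two primaries in one of two ways:
   - Fixed sequence: ROS at .05, then cortisol at .05 only if ROS is significant. The powered test loses nothing; cortisol cannot be claimed if ROS fails.
   - Holm across the two, with the first step at .025. Either outcome can then succeed, at the power cost in step 5 of the working. The planned minimum of 20 groups would just cover that step for ROS at r = 0 with no clustering.
4. Label H2 to H4, RQ5 and the secondary outcomes as secondary or exploratory, and report them with 95% intervals. Holm over H1 and H2 on both outcomes is possible, but its first step of .0125 takes a test with 80% power to about 62%.
5. Fix one noise predictor now, for example whole-walk traffic L_Aeq, and report the L_AE-plus-proportion form as a sensitivity analysis. Align the other two descriptions of the predictor with it.

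The cost is a few sentences, plus the stricter first step if Holm is chosen.

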## Discussion

This article describes the development and design of a protocol for a randomized, controlled longitudinal intervention study, comparing the effects of walking in forests and urban built environments on restoration, considering road traffic noise exposure during the walks in the respective settings.

Our planned study has several methodological strengths, including a longitudinal design, a multi-method outcome assessment including physiological measures (e.g., salivary cortisol), an attention test, and self-report data. This study extends upon previous studies comparing the effects of walking in greenspaces versus urban built environments by controlling for the potential detrimental effects of different road traffic noise levels in the environments. Since previous studies on the effects of noise on stress have often been based on laboratory [44, 51, 55–57] or cross-sectional data [41, 43, 53, 54], this study contributes to emerging research in providing data from a longitudinal field study. Unlike previous studies, which only assessed noise at one representative point on each route in each environment [40], noise will be measured continuously throughout every walk to assess the effect of the effective noise in the actual moment of the walk.

Further, rather than focusing on restoration from a stressed or depleted state, we will explore the instorative effects of walking in different environments with participants who have not undergone a prior stress intervention [104, 105]. Many previous studies have examined restoration after stressing participants [68, 74, 106, 107], which makes it easier to find greater restoration effects because of a higher baseline level of stress and attentional fatigue [89, 104]. However, the aim of this study is to examine the potential of walking in different environments for the psychophysiological wellbeing of individuals with an ecologically valid amount of stress and the need for restoration in their everyday life, without an artificial induction of stress or fatigue. This is because we focus on exposure to greenspaces as a low-threshold approach in the general public, not merely focusing on reducing stress and restoring depleted attentional resources but also on fostering wellbeing.

This study also has some methodological limitations. First, while we expect the settings in noisy conditions to display higher mean noise values compared to relatively quiet conditions, mean noise levels in urban built settings are expected to be systematically louder than in forest settings. When beginning the process of selecting the test sites, we aimed to apply the same noise thresholds in terms of dBA for loud and quiet urban built and forest settings for the GIS analysis, as we wanted to compare these. During the selection process of the test settings, however, it became clear that defining loud and quiet depends on the context of the site, with mean noise levels in urban built environments being, on average, higher than in forest settings (see Table 2). This systematic difference between urban built environments and forests, however, if not explicitly accounted for in the statistical model, might result in a potential systematic confounding of noise level and setting category (urban built or forest). We therefore plan to account for this by including noise as a continuous predictor in the second model, as discussed above. However, this must be considered in the data analysis and interpretation of the study results.

Second, because noise features high situational variance, finding situations with widely constant noise conditions was a major challenge. Thus, the noise variance within each setting will have to be considered and discussed along with the final data analysis. The same also applies to seasonal differences in the vegetation and thus in VHM and NDVI.

Third, it is important to note that without further information on the type of sound source, dB values possess only limited potential to predict noise annoyance and consequently stress. The assessed noise levels during the walks will partly reflect sound from individual motorized traffic but also other sound sources, such as sounds from people, animals, wind, and moving leaves from trees. The research team, with expertise in both environmental and health psychology as well as acoustics research, carefully discussed these limitations during the study design process; however, there is no viable way to fully avoid them in a field study. Therefore, we plan to account for this by extracting the percentage of time, during which road traffic noise is the dominant sound source in the sound measurements of every walk, as well as by including the *L*_Aeq_ during the time when road traffic noise is the dominating sound source as predictors for the statistical model. Fourth, especially when measuring sound during the walks in the forest settings, the sound of the experimenter walking partly masks other, quieter, or more distant sounds. Thus, the *L*_Aeq_ from such sounds (e.g., natural sounds) during the walks cannot be extracted from the recordings. However, because traffic noise is usually louder than the walking sound, this will only be a minor source of uncertainty regarding the recorded road traffic *L*_Aeq_ during the walks.

Finally, for individuals working full time, who could be hypothesized to be the ones with the highest stress levels, it might be difficult to find a convenient, appropriate, or suitable time slot, since walking sessions only take place in the afternoon.

The results of this study will inform us about the restorative effects of exposure to different types of landscape environments and to different road traffic noise levels at these sites. Through the methodology of this study, this research not only adds to the body of literature on the topic, but also provides an improved foundation for practical applications. The study will add information about the benefits of walking and nature-based interventions as well as their potential to reduce stress and promote wellbeing, thus facilitating a better understanding of low-threshold interventions to prevent stress and foster wellbeing. In addition, the results will have the potential to inform noise legislation and the implementation of spatial planning acts.

## Data Availability

The data from the setting selection process is publicly available on the Open Science Framework under https://osf.io/2bfgv/. The final dataset of the study will be made publicly available in the results publications.
